### Setting

2.3

This study will be undertaken in two RAC homes in metropolitan South Australia. These facilities are run by a not‐for‐profit organisation and provide three levels of support for people with dementia and complex needs. Site 1 has 115 residents, with eight residents in a Specialist Dementia Care Unit with severe behavioural and psychological symptoms of dementia and three memory support units for residents with dementia (two with nine residents and one with 15 residents). Site 2 has 76 residents with nine residents in a memory support unit.

At each site, person‐centred care is delivered by teams with a skill mix, which includes a clinical care manager, clinical nurse, registered nurse, enroled nurses, personal care workers and lifestyle assistants. Additional staff include the Hotel Services team including kitchen hands, cleaners, administration and maintenance staff, who interact with residents without providing personal care. Nurses are registered with the Australian Health Practitioner Regulation Agency and personal care workers and lifestyle assistants require a minimum of Certificate III Individual Support or similar. The Specialist Dementia Care Unit receives additional support from a nurse consultant employed by a local health network older persons’ mental health service.

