**Quantitative Data**
1.Routinely collected data pertaining to pro re nata (PRN) psychotropic medication use (from the organisation's psychotropic register where nursing staff record PRN psychotropic medication) and inappropriate restrictive practice incidents (as reported via the Serious Incident Reporting Scheme‐SIRS) will be collected by staff from the aged care organisation and forwarded to the research team for analysis. The total number of PRN psychotropic medications used and restrictive practice events on each individual resident will be calculated over three time periods, which are (1) 12 months before the implementation of the Safewards programme; (2) from start to completion of the programme (3 months) and (3) 3‐months post the completion of the programme. The average use of PRN psychotropic medications for each individual resident per time period, and the total number of restrictive practice events per individual resident per period will be calculated. The difference between the medication usage and a number of events before and after the implementation of the programme will be analysed using the analysis of variance method. The Australian Aged Care Quality & Safety Commission govern the SIRS, which aims to identify and prevent abuse and neglect among people receiving aged care. As only ‘inappropriate’ restrictive practice use is reportable to SIRS, and there is a very low reporting rate sector wide (e.g., < 200 reports of inappropriate restrictive practice use across the entire Australian RAC sector in the October–December 2023 quarter), these data are likely to be limited.2.Surveys (preimplementation and 1 month postimplementation) exploring staff confidence, motivation and uptake of nonrestrictive practices will be forwarded to all aged care staff (*n* = 200). Surveys have been adapted from the Victorian trial (Appendix S2). All data will be de‐identified. Staff will be asked to identify site location and provide a unique identifier to allow for pre‐ and postdata to be combined. Comparisons will be made pre‐ and post‐Safewards implementation. The online platform Qualtrics will be used to collect survey data.3.Routinely collected data pertaining to resident satisfaction with care and quality of life is routinely collected by the organisation for reporting purposes (https://www.qol-acc.org/). The most recent survey data available before the intervention and at the completion of implementation phase will be used for analysis.4.Routinely collected data pertaining to staff satisfaction (from a staff satisfaction survey developed by Willis Towers Watson) and staff injury (via the Injury Management platform). All data will be de‐identified by staff working in the aged care organisation. The most recent survey data available before the intervention and at the completion of implementation phase will be used for analysis.5.The Victoria Safewards fidelity scale (https://www.safewards.net/managers/evaluation-methods) will be adapted for the setting and completed by two members of the research team on completion of the implementation phase and 3 months postimplementation. The fidelity scale reports on the number and quality of interventions that have been implemented.

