
We will analyse the data based on the available information on PRN psychotropic mediation and restrictive practice events. No imputation method will be applied due to the high possibility of introducing bias. For all the surveys, the incomplete information will be treated with appropriate imputation techniques consistent with the scoring protocol of the respective survey.

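### Per-resident averages and totals over windows of 12, 3 and 3 months let resident turnover move the before/after comparison without any programme effect

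*Protocol article*

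**What the plan says.** Section 2.9 of the protocol article, Quantitative Data item 1, takes PRN psychotropic use from the organisation's register and restrictive practice incidents from routine reports. PRN use is summarised as "The average use of PRN psychotropic medications for each individual resident per time period". For restrictive practice, "the total number of restrictive practice events per individual resident per period will be calculated". The baseline window is "12 months before the implementation of the Safewards programme"; the programme window lasts 3 months; the last window is "3‐months post the completion of the programme". The difference "before and after the implementation of the programme will be analysed using the analysis of variance method". The text does not say whether this is a one-way or a repeated-measures analysis.

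The closing paragraph on quantitative data adds: "We will analyse the data based on the available information on PRN psychotropic mediation and restrictive practice events", and rules out imputation for these two outcomes. Section 2.3 gives 115 residents at site 1 and 76 at site 2, 191 in all. They include "eight residents in a Specialist Dementia Care Unit" and 42 in memory support units (9 + 9 + 15 at site 1, 9 at site 2). Table 3 uses both outcomes to look for early indications of effect. Section 3.3 names the short timeframe and sector reform as limitations, not resident turnover.

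**The concern.** In an aged care home people die, leave and are admitted throughout. When the resident is the unit, someone present for 20 days weighs as much as someone present all year. The 12-month window collects about four times as many leavers and entrants as a 3-month window, so the two means are taken over differently composed groups even when nothing about care or case mix has changed.

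This is separate from the unequal window lengths. Scaling a total by calendar time does not cure it, because many residents were not present for the whole window. Dividing each resident's count by that resident's own days does not cure it either, because the unweighted mean still over-represents short stays, and more so in the longer window. At stake is the before/after estimate for PRN use and restraint, which the study will read as a possible signal and use to inform a later effectiveness trial.

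**Working it through.** The plan states no sample size, effect size or turnover figure for these outcomes, so there is no figure of its own to reproduce.

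**Inputs from the documents:** 115 + 76 = 191 residents; windows of 12, 3 and 3 months.

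**Assumptions:** full occupancy; a constant share t of 20-40% of residents replaced per year; no programme effect; where stated, use 2 or 3 times higher in the last 60 days of stay.

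**1. Who contributes.** A window of L years has about 191(1 + tL) contributors, of whom 191tL leave during it. The leavers' share is tL/(1 + tL).
- 12 months: 0.20/1.20 = 17% to 0.40/1.40 = 29%.
- 3 months: 0.05/1.05 = 5% to 0.10/1.10 = 9%.

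**2. Per-resident totals, scaled only for window length.** With a constant event rate λ, events in the window are 191λL. The mean per resident is λL/(1 + tL), and after scaling λ/(1 + tL). The ratio of post to baseline is (1 + t)/(1 + t/4):
- t = 20%: 1.20/1.05 = 1.14
- t = 30%: 1.30/1.075 = 1.21
- t = 40%: 1.40/1.10 = 1.27

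This is a spurious rise of 14-27%.

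**3. Per-resident rates (each count over the resident's own days).** Take t = 20%. For a resident who leaves at a uniformly distributed time in a window of W days, the expected fraction of observed days that fall in the last 60 is (60/W)(1 + ln(W/60)): 0.461 for W = 365 and 0.934 for W = 91.
- Times the leavers' share: 0.167 × 0.461 = 0.077 at baseline; 0.048 × 0.934 = 0.044 post.
- Residents who leave within 60 days after the window closes number 191 × 0.20 × 60/365 = 6.3, with about 30 such days inside the window. They add 6.3/229 × 30/365 = 0.002 and 6.3/201 × 30/91 = 0.010.
- Sums: about 0.079 and 0.055. With doubled use the ratio is 1.055/1.079 = 0.98; with tripled use, 1.110/1.158 = 0.96.

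This hand count leaves out people admitted and gone within one window, who add more to the longer window. Simulation includes them.

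**4. Simulation.** 191 beds, 365-day baseline, 91-day post window starting 91 days later, 400 runs per scenario. Mean ratio of post to baseline under no effect:

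| Turnover | Totals scaled for window | Per-resident rates, use ×2 | Per-resident rates, use ×3 | Events over resident-days | Present in both, ×2 | Present in both, ×3 |
|---|---|---|---|---|---|---|
| 20% | 1.14 | 0.97 | 0.95 | 1.00 | 1.06 | 1.11 |
| 30% | 1.21 | 0.96 | 0.93 | 1.00 | 1.08 | 1.16 |
| 40% | 1.27 | 0.96 | 0.92 | 1.00 | 1.11 | 1.22 |

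Without end-of-stay excess, the rate, pooled and present-in-both ratios are all 1.00. The totals ratio is unchanged.

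**5. What the pooled rate does not cure.** If a share t leave with r times the use of those who stay or replace them, the case mix itself changes, and the change is 1/((1 - t) + tr) - 1. At t = 20% and r = 2 this is 1/1.20 - 1 = -16.7%, and the pooled rate shares it. The sign reverses if entrants are the heavier users.

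**The case against.** The strongest reply is that an article may leave the cohort definition to a fuller document, and that the available-data sentence is a missing-data rule, not a definition of who is analysed. That is right, and the missing cohort definition is not the point here. A reader might infer that the plan expressly pools whoever was present in each window, but the text does not say so. The unnamed form of analysis of variance also allows a repeated-measures reading. That reading would hold the composition fixed, but only by restricting the result to residents who stayed, and in the end-of-stay scenario that comparison is biased upward. Neither reading gives a clean signal.

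Other stronger claims also fail:
- Both outcomes are not averaged per resident. Restraint events are totalled; the analysis then compares period means of those totals.
- These are not the only quantitative resident outcomes. Item 3 of the same list adds satisfaction and quality of life.
- The documents say that findings will inform a future trial, not that its baseline or variance figures will come from here.
- Use concentrated in a few residents is not a further bias. With assumed relative rates of 10, 3 and 1 in the specialist unit, memory support units and elsewhere (8, 42 and 141 residents) and no effect, the mean ratio was 1.00 over 500 runs. The 95% range at 40% turnover was 0.85-1.17 for per-resident rates and 0.87-1.14 for the pooled rate. That is chance spread, and the pooled rate barely narrows it.

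It is also fair that this is a pilot with no decision rule resting on the test. In a simulation in which the case mix itself changed (26% heavy users at the start, 13% among entrants), one-way analysis of variance gave false-positive rates of at most 7%, except 24% at 40% turnover with a five-fold rate ratio. The harm lies mainly in the estimate.

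**Conclusion.** The point holds as a should-fix item, with medium confidence. The stated per-resident summaries respond to turnover, and the direction depends on how the average is formed: a rise of about 14-27% for totals scaled by calendar time, or a fall of about 3-8% for per-resident rates. The same null data could therefore look like harm or benefit. These figures assume 20-40% annual turnover, and the second also assumes use 2-3 times higher in the last 60 days of stay. Neither assumption comes from the documents. With no end-of-stay excess, the per-resident rate is not biased. Events over resident-days are unaffected under stable turnover and case mix. A reader might infer that a fall in PRN use after Safewards would be a turnover artefact; the documents do not support that, since the true size and sign are unknown.

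**What to change.** In section 2.9, Quantitative Data item 1:
- Make total events divided by total resident-days in each period, over all residents present, the main summary for both outcomes.
- Compare periods with a count model that has a log resident-days offset and allows for repeated periods within resident. One option is a log-link generalised estimating equation with independence working correlation and resident-clustered standard errors, whose point estimate is the pooled rate ratio.
- Report the numbers of residents entering and leaving in each period.
- Give the comparison among residents present both before and after as a sensitivity analysis only, labelled as a survivor comparison that can be biased upward.
- State that the pooled rate does not remove real changes in case mix, or chance variation from a few high users.

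Cost: wording, plus admission and departure dates and a pseudonymous resident code in the de-identified extract that the organisation already prepares. The consent waiver described in section 2.10 does not list these items, so a minor ethics amendment may be needed; the eight-resident unit calls for care over re-identification.

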#### Implementation Phase

2.6.3

Implementation of Safewards at each site will occur over 12 weeks. The clinical educator from the aged care organisation and two trainers from the project team (one staff with lived experience of caring for a family member with dementia) will provide on‐site training of aged care staff. An online community of practice groups will be established to share learnings and support implementation across sites.

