#### Evaluation Phase

2.6.4

Programme evaluation will examine the impact of Safewards in aged care homes, and identification of successful implementation strategies and adaptations made to the interventions for service fit. Further details of the outcomes evaluation are provided in Table 3.

**Table 3 hex70037-tbl-0003:** Evaluation summary.

**RE‐AIM domains**	**Evaluation aims and outcome measures**
*Reach:* Participation in the intervention (individual level)	*Aim*: To describe the number, proportion and characteristics of staff who are willing to participate in the intervention. *Data collection: Quantitative*—Number of staff who engaged in the training and participant characteristics (age, gender, qualifications and cultural background).
*Effectiveness*: Impact of the intervention (individual and setting level)	*Aim:* To determine the appropriate and feasible effectiveness outcome measures and potential signals of effect. 1. *Resident outcomes. Data collection: Quantitative*—Pre‐ and postquarterly reports of pro‐re‐nata psychotropic medication use, pre‐ and postquarterly reports of incidents of mechanical, physical and environmental restraint. *Qualitative*—Interviews postimplementation to understand the experiences of the intervention. 2. *Family member outcomes. Data collection: Qualitative*—Interviews postimplementation to understand experiences of the intervention. 3. *Staff outcomes. Data collection: Quantitative:* Pre‐ and postsurveys to assess levels of confidence and capacity to support residents with complex needs and use the intervention, pre‐ and postsurveys to assess staff well‐being. *Qualitative*—Focus groups (or interviews) to understand experiences of the intervention.
*Adoption:* Degree of uptake of intervention (individual and setting level)	*Aim:* To describe the number, proportion and representativeness of staff and settings who delivered the intervention. *Data collection: Quantitative*—Setting exclusions/inclusions (% units and reasons); staff exclusions/inclusions (% of staff invited that participate in training); degree of implementation of Safewards (number of interventions implemented). *Qualitative*—Focus groups (or interviews) to understand staff perceptions of barriers and enablers to setting‐ and staff‐level adoption.

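### Restrictive practice events are totalled over a 12-month baseline and two 3-month windows and compared without a time denominator, so an unchanged rate shows as a fall of up to 75%

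*Protocol article*

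**What the plan says.** Section 2.9 (Quantitative Data, item 1) defines the baseline period as "1) 12 months before the implementation of the Safewards programme". The two later periods each last a quarter of that: one spans the programme itself and the other follows it. Section 2.6.3 agrees on the length of the programme: "Implementation of Safewards at each site will occur over 12 weeks".

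For restrictive practice events the measure is a raw sum: "the total number of restrictive practice events per individual resident per period will be calculated". For PRN psychotropic medication the same sentence uses an average per resident per period and gives no unit of time. The differences before and after implementation then go into an analysis of variance.

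On incomplete data, section 2.9 says: "We will analyse the data based on the available information on PRN psychotropic mediation and restrictive practice events". It rules out imputation for these outcomes and says nothing about how long each resident was in the home.

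Table 3 (section 2.6.4, Effectiveness) describes the data as pre and "postquarterly reports of incidents of mechanical, physical and environmental restraint".

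**The concern.** A count grows with the time over which it is collected. A 12-month count and a 3-month count of the same process differ fourfold in expectation even if nothing has changed. Here the longer window is the baseline, so the artefact runs in favour of the programme.

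The article does not leave the measure open for a later document to fill in. It names the total, the unequal windows and the test. A later plan would have to depart from this sentence to repair it.

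The stakes are those of a pilot, but they are real. Table 3 looks for possible signals of effect, section 2.1 says the findings will inform a future effectiveness trial, and section 3.3 links evidence of positive impact to wider roll-out. Even a purely descriptive table of these totals would suggest a large reduction.

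**Working it through.** The article states no expected change, sample size or power for this outcome, so there is no figure of its own to reproduce.

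**Inputs from the article.** Windows of 12, 3 and 3 months (section 2.9). Residents: 115 + 76 = 191 (section 2.3). Fewer than 200 reports of inappropriate restrictive practice in one quarter across the Australian sector (section 2.9), and about 191,000 people in residential aged care (section 1).

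**Step 1: expected totals with no change.** With a constant rate of r events per resident-month and full presence, the expected totals per resident are 12r, 3r and 3r. The ratio of either later window to baseline is 3r/12r = 0.25, so the apparent fall is 1 − 0.25 = 75% for any r. For example, r = 0.5 gives 6.0, 1.5 and 1.5 events. The true rate would have to rise fourfold for the totals to look unchanged.

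**Step 2: shorter presence in the baseline.** Residents admitted during the baseline year contribute less than 12 months to it. The article gives no turnover figures, so the mean months present are assumptions. The apparent fall is 1 − (post months / baseline months).

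| Baseline / post months present (assumed) | Apparent fall |
|---|---|
| 12 / 3 | 75% |
| 10 / 3 | 70% |
| 9 / 3 | 67% |
| 6 / 3 | 50% |

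**Step 3: event rate implied by the article for reportable incidents.** As an upper limit, 200 / 191,000 / 3 = 0.00035 per resident-month. For 191 residents this is 0.00035 × 191 × 12 = about 0.8 events in 12 months, and about 0.2 in 3 months, if these homes match the sector.

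**Step 4: how often the test would reject with no effect.** Simulation assumptions: 191 residents, overdispersed (gamma-Poisson) counts with shape 0.25, full presence, no clustering by unit, repeated-measures analysis of variance, significance level 0.05.

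| Events per resident-month | Rejection on totals |
|---|---|
| 0.1 or more | 100% |
| 0.02 | 99.7% |
| 0.01 | 93% |
| 0.005 | 70% |
| 0.002 | 32% |
| 0.00035 (sector-wide reportable rate) | about 3% |

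With variation between units added, and with one-way or repeated-measures analysis of variance, rejection at 0.02 to 2 events per resident-month stayed at 95% to 100%.

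**Step 5: same data on a common time unit.** Dividing each count by its window length gives an expected ratio of 1.00, a change of 0%. Rejection with no effect then falls to about 5% to 6% at rates of 0.005 and above.

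**The case against.** **The events may be too rare for a false positive.** Section 2.9 takes the events from the Serious Incident Response data and itself warns that they will be limited. This objection stands against the test. A reader might infer that the analysis will report a significant reduction whether or not the programme works. The article does not support that: at the sector-wide reportable rate the test rejects in only about 3% of runs, and a rate of 0.02 is about 57 times higher (0.02 / 0.00035). The objection does not rescue the measure, because the expected totals are biased at any rate. Section 2.10 also names internal incident report forms as a source. These could yield more events, at a rate the article does not give.

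**PRN use is described as an average.** This also stands. A reader might extend the 75% to PRN medication. The wording sets an average for PRN use against a total for events, and the average could reasonably be read as scaled for time. The fault there is an unstated unit, not a demonstrated bias.

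**Table 3 refers to quarterly reports.** A reader might see an outright contradiction with the 12-month total. That is too strong, since four quarterly reports can be summed to a year. But Table 3 describes what is collected and does not say that the analysis uses quarterly values, so it supplies no denominator either.

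**This is a feasibility pilot, and a condensed article need not give model details.** The choice of count model, offset and coding of residents without events can fairly be left to an analysis plan. Comparing totals over unequal windows is a stated rule, not an omitted detail.

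**Conclusion.** The point holds for restrictive practice events: the comparison is wrong as written. With a constant rate and full presence, the expected later total is 25% of baseline, an apparent 75% fall. Under the assumed shorter baseline presence the apparent fall is about 50% to 70%, so turnover of this kind shrinks the artefact without removing it.

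The effect on the significance test depends on event frequency. Rejection is nearly certain at 0.02 or more events per resident-month and about 3% at the sector-wide reportable rate, where the damage is confined to the descriptive totals. These rejection rates rest on the assumed overdispersion and significance level. The 3/12 ratio does not.

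PRN use and Table 3 are secondary: one needs its time unit stated, the other needs to agree with section 2.9.

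**What to change.** In section 2.9, item 1, replace the total number of events per period with events per resident-month (or per quarter, or per 1,000 resident-days), using the same unit in all three periods. Preferably take each resident's days in residence within each period as the denominator, or as the offset if a count model is used. Dividing by window length alone removes the 12-versus-3-month artefact; days in residence also deal with admissions, departures and deaths.

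State the same time unit for average PRN use, and make the unit in Table 3 match section 2.9.

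The cost is a change of wording in two places, plus occupied days, or admission and exit dates, from the organisation's staff who already extract the data. Nothing further is needed from residents.

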In Australia, despite policy commitment, the acknowledged harms and multiple reviews recommending reduced reliance on restraints, restrictive practice remains prevalent in aged care homes [3]. Quality indicators for RAC in Australia report that the current rate of restraint use (including physical, mechanical and environmental restraint and seclusion) is 18.1% (a decrease of 23% from 12 months earlier) [13]. Research into restrictive practices in aged care homes shows that restraint use is influenced by a range of factors, including legislation and policy, and resident, staff and job characteristics [11]. The overuse of restraints in aged care has been found to be related to systemic issues rather than clinical needs, specifically inadequate staffing (skill mix and levels) and training [3, 8]. Proposals for reducing restrictive practice use include addressing attitudes and culture, enhancing training and education and reforming legislation and policies [14]. Several recent systematic reviews have examined interventions aimed at reducing physical restraint use in RAC [15, 16, 17]. Overall, there appears to be more evidence for multicomponent interventions (e.g., policy changes and education) rather than education alone [15, 16]. Strategies/interventions developed specifically to reduce overprescribing of psychotropic medication (a common restrictive practice) in RAC are also often multicomponent [18]. Previous studies have focused on training nursing staff and rarely include the voices of residents [15, 16]. To date, in Australia, reforms aimed at minimising restraint use have focused on amendments to legislation and policy [19, 20]. For example, aged care providers must monitor, review and report restraint use. Although providers are required to reduce restrictive practice use, there remains a gap in knowledge about the most effective strategies/interventions to achieve sustained reduction in restraint use in RAC. This study will extend current knowledge by testing a programme aimed at reducing conflict and restraint use. Training will be provided to personal care workers, who are the majority workforce in RAC in Australia, and residents will be included in the evaluation.

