#### Site Preparation and Training

2.6.2

This stage includes in‐depth 2‐day training for key staff members at the participating sites (including managers, educators, nurses and aged care workers), identification of staff to lead the range of interventions and co‐development of an implementation plan for each site. Implementation plans/processes (e.g., Safewards interventions readiness checklist) from Safewards UK will inform implementation. Adaptations/tailoring of the Safewards interventions will be discussed at a weekly implementation working group, held with the trainers and research team and key organisational staff (e.g., clinical care managers and the clinical educator; Table 2). An expert in Safewards will provide ongoing mentoring for the project duration via teams. Details of this will be determined by key staff at the RAC home.

**Table 2 hex70037-tbl-0002:** Implementation strategies.

**Implementation strategy**	**Example**
Evaluative and iterative strategies 1. Assess for readiness and identify barriers and facilitators 2. Purposefully re‐examine implementation 3. Develop and implement tools for quality monitoring	Weekly implementation working group identifies barriers/facilitators and reports to Steering Committee. Evaluation process. Adapt and use Safewards Fidelity Checklist.
Develop stakeholder interrelationships 1. Identify and prepare champions 2. Organise implementation teams 3. Obtain formal commitments 4. Capture and share local knowledge 5. Use advisory boards and workgroups 6. Develop academic partnerships	2× champions for each intervention at each site. Champions to meet as a group at each site. Executive sponsorship obtained. Weekly implementation working group with participants from across both sites and implementation of a Community of Practice. Weekly implementation working group. Project occurring in partnership with the University.
Train and educate stakeholders 1. Develop educational materials 2. Conduct educational outreach visits	Facilitators (from the research team) adapting Safewards materials in collaboration with key staff from the aged care organisation. Facilitators (from the research team) and clinical educator from the aged care organisation providing education on each intervention to aged care staff.
Engage consumers 1. Involve residents and family members	Invitation for involvement in steering committee, participation in selected interventions and evaluation.

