### Strengths and Limitations of the Study

3.3

To our knowledge, this will be the first study to report on the impact and implementation of the Safewards programme into RAC. If this pilot trial demonstrates evidence of positive impacts for residents, families and/or staff, further roll‐out of Safewards across RAC has the potential to positively address the issue of overuse of restrictive practices. Regardless, findings from this study will inform future implementation strategies of novel interventions in RAC. This includes testing the feasibility of data collection to answer the research questions. The limitations include the 12‐month project timeframe and the extensive reform that is currently taking place in the aged care sector resulting in a range of changes in service provision. Although the latter can be viewed as a potential facilitator, there are currently significant demands on RAC to align service provision to the recommendations from the Royal Commission.

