## Conclusion

4

Restrictive practice use is a complex problem requiring sustained attention, co‐production and testing of multicomponent interventions [53]. To promote the rights, freedoms and dignity of people living with complex needs in aged care, approaches that are feasible, effective and sustainable are urgently needed [54]. This project will extend the investigation of Safewards and test the implementation of the model and interventions in two RAC homes. Project findings will provide an in‐depth understanding of the successful implementation processes, the impact of Safewards in reducing restrictive practices and recommendations for wider implementation of Safewards across RAC. The benefits of this project include building the competencies of the aged care workforce and improving the quality of life for people living with dementia and other complex needs in RAC homes.

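### The before/after comparison has no trend term or benchmark, so for restraint incidents expressed as rates a fall of roughly 13–23% could appear with no Safewards effect

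*Protocol article*

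**What the plan says.** Section 2.9 of the protocol article (Quantitative Data, item 1) defines three windows: "12 months before the implementation of the Safewards programme", the 3-month programme, and the 3 months after completion. For each resident and window it takes the average PRN psychotropic use and the total number of restrictive practice events. It then says: "The difference between the medication usage and a number of events before and after the implementation of the programme will be analysed", by analysis of variance. Both homes receive the programme (Abstract, 2.3). No control home, time trend or external reference is mentioned.

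Three other places bear on this:

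- The Introduction gives the sector position: "current rate of restraint use (including physical, mechanical and environmental restraint and seclusion) is 18.1% (a decrease of 23% from 12 months earlier".
- Section 3.3 lists as a limitation "the extensive reform that is currently taking place in the aged care sector resulting in a range of changes in service provision". It does not connect this to the before/after analysis.
- The Conclusion (section 4) says the findings will provide an understanding of "the impact of Safewards in reducing restrictive practices and recommendations for wider implementation".

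**The concern.** An uncontrolled before/after contrast implicitly takes no change as its no-effect reference. The article's own background says restraint was already falling across the sector, and that the reforms which may be driving this continue. Averaging the baseline year into one value has two consequences. The baseline carries older, higher rates, and the information that would show whether the rate was already declining before Safewards is lost.

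At stake is the reading of the effectiveness result. Table 3 seeks potential signals of effect, 3.3 links evidence of positive impact to further roll-out, and section 4 speaks of impact. A signal needs a credible no-effect reference. Naming reform as a general limitation does not supply one.

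**Working it through.** The article gives no effect size or power figure to reproduce. The check asks what the planned contrast would show if Safewards did nothing and the sector trend applied.

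**Inputs**
- Sector restraint indicator: 18.1%, down 23% in 12 months (Introduction). Read as a relative fall, the earlier level was 18.1/0.77 = 23.5% and the annual ratio is 0.77.
- Windows in months from programme start (2.9): baseline −12 to 0, programme 0 to 3, post-programme 3 to 6. Midpoints: −6, 1.5 and 4.5.
- Assumption: events are expressed as rates per unit of time.

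**Constant proportional decline that continues**, rate(t) = 0.77^(t/12):
- Baseline mean: (1/0.77 − 1)/(−ln 0.77) = 0.2987/0.2614 = 1.143.
- Programme window: mean 0.968; ratio to baseline 0.847; fall 15.3%.
- Post-programme window: mean 0.907; ratio to baseline 0.793; fall 20.7%.
- Midpoint check, 10.5 months apart: 1 − 0.77^(10.5/12) = 20.4%.

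**Other shapes of the trend, post-programme against baseline**
- Linear, falling from 1 to 0.77 over the baseline year and continuing: 1 − 0.684/0.885 = 22.7% (programme window 16.2%).
- Linear, with a slope of 23% of the starting level per year: 1 − 0.914/1.115 = 18.0% (programme window 12.9%).
- Decline stops at programme start: 1 − 1/1.143 = 12.5% (proportional) or 1 − 0.77/0.885 = 13.0% (linear). Some fall remains because the baseline average includes the earlier, higher months.

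**Other assumed annual declines** (midpoint formula): 5% gives 4.4%, 10% gives 8.8%, 15% gives 13.3% and 30% gives 26.8%.

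**Last pre-programme quarter as baseline:** the midpoints are 6 months apart, so 1 − 0.77^(6/12) = 12.3%. Shortening the baseline reduces the artefact but does not remove it.

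**SIRS events.** Section 2.9 gives fewer than 200 reports of inappropriate use per quarter across the sector, the Introduction about 191,000 residents, and 2.3 gives 115 + 76 = 191 residents in the two homes. At the sector rate, 200 × 191/191,000 = 0.2, so fewer than 0.2 events are expected per quarter and fewer than 0.8 in the baseline year.

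**PRN psychotropic use.** The article gives no trend, so no corresponding figure can be computed.

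**The case against.** The strongest reply is that the 23% does not describe either outcome named in the analysis sentence. It is a sector quality indicator for physical, mechanical and environmental restraint and seclusion. Section 2.9 analyses PRN psychotropic use and inappropriate incidents reported through SIRS. This stands. A reader might infer that the whole comparison carries a 20% bias, and the document does not support that. The figure bears on restraint incidents as Table 3 and 2.10 describe them (physical, mechanical and environmental, with 2.10 naming internal incident forms). Even there, carrying it over to two homes is an assumption.

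Other points also have weight:

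- One 12-month change is not an established annual rate, hence the range above.
- The arithmetic presumes rates, while 2.9 specifies event totals over unequal windows. Raw totals over 3 rather than 12 months would fall by 1 − 3/12 = 75% with no trend and no effect.
- Fewer than 0.2 expected SIRS events per quarter cannot support a segmented model, and 2.9 already warns that these data are likely to be limited. With three post-programme months, such a model is thin for PRN use too.
- A reader might infer that staff training inside the baseline adds to a bias favouring Safewards. Section 2.6.2 places the 2-day training in the preparation stage, so it may precede the programme window, but the article text does not date it and Figure 1 is not shown. If that training reduced restraint, it would lower the baseline and dilute an effect.
- Table 3 seeks only feasible measures and potential signals, effectiveness is left to a future trial, and no progression rule rests on this contrast. It would be too strong to say that a fall would be credited to Safewards. It could be, given the wording of 3.3 and section 4.

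What does not stand is that pilot status, or the general limitation in 3.3, settles the matter. Neither gives the reader a no-effect reference for the contrast.

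**Conclusion.** The concern holds for restraint incidents expressed as rates. With no Safewards effect, the planned contrast could show a fall of about 13–23% in the post-programme window: about 20% if the quoted sector decline continues in these homes, and about 13% if it stops at programme start. For the programme window the figure is about 15% if the decline continues. These figures are illustrative. They assume that the 23% is a relative fall, that it carries over to incident rates in these two homes, and that rates rather than raw totals are compared.

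For PRN psychotropic use the comparison is equally uncontrolled, but neither the size nor the direction of any bias can be derived from the document. For SIRS events the counts are too small for a trend of this size to be visible. The document therefore does not show that a null programme would produce a 20% fall across the outcomes. It does show a contrast whose no-effect value for restraint is not known to be zero change, next to wording that promises impact. The sponsor should correct this, and the correction is inexpensive.

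**What to change.** - Replace the single 12-month value with quarterly rates per resident-time (for PRN use, monthly if the register allows), and display the pre-implementation trend.
- Show restraint rates beside the sector quality indicator for the same quarters.
- Add a pre-existing slope term only where counts support it, realistically PRN use, and label it exploratory. Do not model SIRS events this way.
- State whether the baseline ends before the first 2-day training, and note that any overlap would dilute an effect.
- Reword section 4 so that it promises a signal of change that cannot be attributed to Safewards without a comparator.

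No new sites or participants are needed. Table 3 already refers to quarterly reports. Monthly counts and resident-time are not mentioned, so the organisation would have to confirm that it can supply them. The price is wider intervals, since a slope would be estimated from few points, and a weaker claim.
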